### Statistical analyses

#### Clinical analyses

All statistical analyses will be performed based on intention-to-treat (ITT) principle. Patterns of missing data will be examined and analyses will be corrected for missing data by applying multivariate imputation according to Van Buuren and Groothuis-Oudshoorn [117]. For those who substantially completed the intervention (at least 80% of the modules) additional per-protocol (PP) analyses will be conducted. Group difference between pre- and post-assessment nine weeks after randomization (T1) in primary outcome will be assessed using generalized linear modelling. Between-group effect size will be reported using standardized mean differences and 95% CIs at all measurement points. Reliable change index (RCI) and number needed to treat (NNT) will be calculated to determine clinical significance. Analysis of long-term effects will be adjusted to the data structure by using e.g. robust estimation of standard errors or mixed effect modelling. Group differences in depression onset will be assessed by calculation of a Poisson regression model. Incidence of clinical depression will be compared in IG and CG by calculation of incidence rate ratio (IRR). Other secondary outcomes like perceived stress, sleep quality, and quality of life will be analysed similarly as primary outcome. Additionally, moderation and mediation analyses will be performed.

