### Objective and research question

The aim of the present study is to investigate whether a tailored IMI program targeting a variety of specific complaints associated with clinical depression is useful in reducing depressive symptoms and preventing onset of clinical depression as compared to enhanced treatment as usual (TAU+) within a 36-month follow-up period. We propose, that depressive symptomology will be reduced to a greater extent in the intervention group (e.g. IMI program) than in the control condition (e.g. TAU+) post-treatment (T1). The following research questions will be investigated in this pragmatic randomized controlled trial over a follow-up period of 36-months:
Is the IMI program effective in reducing depressive symptom severity compared to TAU+?Is the IMI program effective in preventing the onset of clinical depression as compared to TAU+?Is the IMI program effective in reducing various mental health outcomes (e.g. stress, anxiety, insomnia) compared to TAU+?Is there a differential or rather an undifferentiated, general effect of specific IMIs on different mental health outcomes?Is the IMI program superior in terms of cost-effectiveness and QALY health gains compared to TAU+?Which variables moderate and mediate the effects of the IMI program?What is the level of intervention satisfaction, adherence and acceptance to the IMI program?Are there negative effects of the IMI program?

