### Sample size/power calculation

In this trial, the effectiveness of the IMI program in reducing depression severity is compared to TAU+. The estimation of sample size was based on a meta-analysis by Zhou and colleagues (2016) [26], who reported an effect size of *SMD* = 0.46 [95%-CI: 0.22–0.70] for IMIs in the reduction of subclinical depressive symptoms. In this meta-analysis mostly waitlist control groups where included. Since comparison of IG with TAU+ presumably yields a smaller effect size than comparison with waitlist control group [69], we assumed a conservative effect size of *d* = 0.35 for the present trial. An effect size of *g* = 0.35 [95%-CI: 0.23–0.47] was also reported in a meta-analysis as the effect of psychotherapy on reduction of depressive symptom severity in subthreshold depression with more than a half of the included studies applying care as usual in the CG [18]. Based on prior findings [23–25, 48–55], (Ebenfeld L, Lehr D, Ebert D, Kleine Stegemann S, Funk B, Riper H, et al.: Treating panic on the go: results of a randomized controlled trial evaluating a hybrid online-training for panic and agoraphobia symptoms, in preparation) and the above stated hypothesis, a one-sided t-test (α = 0.05; 1-β = 0.90) with a ratio of 1:1 (IG:CG) is used for power calculation. Power calculation was conducted with G*Power (Version 3.1.9.2) and resulted in an overall sample size of 282 participants. According to a meta-analysis approximately 28% percent of dropout occurred across a sample of studies evaluating efficacy and effectiveness of online-based interventions for depression with therapeutic support [69]. To compensate for an expected dropout of 28%, the present study aims at an overall sample size of 360 participants.

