### Assessments

All assessments will be conducted online. For an overview of instruments at screening, baseline (T0), post-treatment (T1), and follow-up assessments (T2-T5), see Table 1. Participants will receive 10€ for completion of each follow-up assessment, starting with T1.

**Table 1 Tab1:** Overview of the assessments

Instruments	Aim	Time of measurement						
		Screening	T0	T1	T2	T3	T4	T5
Screening Instruments								
PHQ-9	Patient Health Questionnaire	✔						
CPG	Chronic Pain Grade Questionnaire	✔						
Chronicity of Pain	Pain longer for 6 months (yes/no)	✔						
Primary Outcome								
QIDS-SR16	Quick Inventory for Depressive Symptomatology		✔	✔^a^	✔	✔	✔	✔
Secondary Outcomes								
Adapted items from CIDI 3.0, CIDI-SC, and Epi-Q Screening Survey	Prevalence of major depression and bipolar disorder		✔	✔	✔	✔	✔	✔
PSS-10	Perceived Stress Scale		✔	✔	✔	✔	✔	✔
ISI	Insomnia Severity Index		✔	✔	✔	✔	✔	✔
GAD-7	Generalized Anxiety Disorder		✔	✔	✔	✔	✔	✔
PAS	Panic and Agoraphobia Scale		✔	✔	✔	✔	✔	✔
MPI	Multidimensional Pain Inventory		✔	✔	✔	✔	✔	✔
NRS	Pain Intensity (0–10)		✔	✔	✔	✔	✔	✔
AUDIT-10	Alcohol use disorder identification test		✔	✔	✔	✔	✔	✔
MBI-GS	Maslach-Burnout-Inventory (subscale emotional exhaustion)		✔	✔		✔		
AQoL-8D	Quality of life		✔	✔	✔	✔	✔	✔
SPE	Subjective prognosis of employment		✔	✔	✔	✔	✔	✔
Cost measurement								
TiC-P	Utilisation of health services, work-related productivity		✔	✔	✔	✔	✔	✔
Intervention-related Outcomes								
WAI-SR^b^, WAI-SRT^c^	Therapeutic relationship			✔		✔		
TAI-OT^b^	Technological alliance			✔	✔			
CSQ-I	Patient satisfaction			✔				
INEP^b^	Inventory of negative effects in psychotherapy			✔	✔	✔		
Negative effects^b^	Negative effects in psychotherapy			✔	✔	✔		
Other assessments								
Other questions	Socio-demographics		✔					
	Predictors for development of major depression		✔					
Diabetes	Diabetes diagnosis (yes/no)		✔					
BDI-II	Suicidality-Item	✔	✔	✔	✔	✔	✔	✔

^a^Primary outcome is the standardized mean difference between intervention and control group at T1. QIDS-SR16 will also be assessed at T0 and T2-T5

^b^Recorded in intervention group only

^c^Recorded in e-coaches only

*T0* Baseline, *T1* 9 weeks, *T2* 6 months, *T3* 12 months, *T4* 24 months, *T5* 36 months

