## Outcome measurements

### Primary outcome

#### Depressive symptom severity at post-treatment (T1)

The primary outcome is depressive symptom severity at post-treatment (T1), assessed with the German Version of the Quick Inventory Depressive Symptomology (QIDS-SR16) [75]. The 16-item self-report inventory covers all nine DSM-5 symptom criterion domains of MDD. The QIDS-SR16 is characterized by high internal consistency of α = .86 [75]. The items are rated on a 4-point-scale ranging between 0 and 3. The total score ranges between 0 and 27, with a higher score indicating higher depressive symptom severity. Whereas a score between 0 and 5 indicates normal health status, scores between 6 and 10 indicate mild depressive symptomology, between 11 and 15 moderate, between 16 and 20 severe and scores greater than 20 indicate very severe depressive symptomology. Since the QIDS-SR16 is sensitive to symptom change and provides very similar results compared to longer clinical ratings like HAM-D17, HAM-D21, and HAM-D24 [75], this inventory will be administered to monitor changes in depressive symptom severity.

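### The primary outcome is the T1 QIDS-SR16 score, but the primary test is worded as a pre-post difference with no baseline adjustment named; the T1 score adjusted for T0 should be specified

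*Protocol article*

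**What the plan says.** All references are to the Protocol article.

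- Primary outcome section: "The primary outcome is depressive symptom severity at post-treatment (T1"), measured with the QIDS-SR16.
- Assessments, Table 1, footnote a: "Primary outcome is the standardized mean difference between intervention and control group at T1". The same footnote confirms that the QIDS-SR16 is also taken at T0.
- Objective and research question: the hypothesis is that "depressive symptomology will be reduced to a greater extent in the intervention group" than under TAU+ at T1.
- Sample size/power calculation: "we assumed a conservative effect size of *d* = 0.35 for the present trial", and "a one-sided t-test (α = 0.05; 1-β = 0.90) with a ratio of 1:1 (IG:CG) is used for power calculation". No correlation between T0 and T1 enters, and the SD that standardises d is not stated.
- Clinical analyses: "Group difference between pre- and post-assessment nine weeks after randomization (T1) in primary outcome will be assessed using generalized linear modelling". The next sentence promises between-group SMDs with 95% CIs at every assessment. The section also says that other secondary outcomes will be handled much like the primary one.
- Covariates: lists moderators and predictors of depression. Baseline QIDS-SR16 is not among them.

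**The concern.** The outcome definition points to the score at T1. The analysis sentence points to the difference between two assessments. Three analyses could claim to be primary: an unadjusted comparison of T1 scores, a comparison of changes from T0 to T1, and T1 adjusted for T0 (ANCOVA). On one data set they give three estimates, three standard errors and three p-values, and the article does not say which one decides the trial.

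The two unadjusted candidates also leave precision unused. The T0 score is collected before randomisation and is likely to predict the T1 score, yet neither uses it well. The T1 comparison ignores it. The change score subtracts it in full, which over-corrects whenever the regression slope of T1 on T0 is below 1. Because the continuous secondary outcomes follow the primary model, the ambiguity carries over to them.

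**Working it through.** **1. Reproduce the plan's figure.** Inputs from Sample size/power calculation: d = 0.35, one-sided α = 0.05, power 0.90, 1:1 allocation. For a two-sample t-test the noncentrality is d·√(n/2), with n per arm. At n = 141 this is 0.35 × √70.5 = 2.94, and exact noncentral-t power is 0.901. The stated result ("resulted in an overall sample size of 282 participants") therefore reproduces as 2 × 141.

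**2. Evaluable number.** The plan states "To compensate for an expected dropout of 28%, the present study aims at an overall sample size of 360 participants". Losing 28% of 360 leaves 360 × 0.72 = 259.2, or 129.6 per arm.

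**3. Variance factors.** Assumptions not in the article: equal SDs at T0 and T1, a T0-T1 correlation r between 0.3 and 0.7, and d expressed in T1 SD units. Relative to the T1 variance:

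- T1 score: 1
- change score: 2(1 − r)
- ANCOVA: 1 − r², with one further degree of freedom used

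The effective d is 0.35 divided by the square root of the factor. At r = 0.3 it is 0.35/√1.4 = 0.296 for change and 0.35/√0.91 = 0.367 for ANCOVA. Multiplying by √(129.6/2) = 8.05 gives noncentralities of 2.38 and 2.95, against 2.82 for the T1 score.

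**4. Power, one-sided 0.05.**

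| r | Change, 259 | T1, 259 | ANCOVA, 259 | Change, 282 | T1, 282 | ANCOVA, 282 |
|---|---|---|---|---|---|---|
| 0.3 | 0.767 | 0.878 | 0.903 | 0.798 | 0.901 | 0.923 |
| 0.4 | 0.821 | 0.878 | 0.922 | 0.849 | 0.901 | 0.940 |
| 0.5 | 0.878 | 0.878 | 0.945 | 0.901 | 0.901 | 0.959 |
| 0.6 | 0.933 | 0.878 | 0.969 | 0.949 | 0.901 | 0.978 |
| 0.7 | 0.976 | 0.878 | 0.989 | 0.984 | 0.901 | 0.993 |

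The change score loses to the T1 score below r = 0.5, ties at 0.5 and wins above it. ANCOVA is highest in every row. Its variance relative to the change score is (1 − r²)/(2(1 − r)) = (1 + r)/2, which is 0.65 at r = 0.3 and 0.85 at r = 0.7. At 259 evaluable, only ANCOVA reaches 0.90 across the whole range.

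**5. Chance imbalance.** The change-score estimate equals the T1 estimate minus the observed group difference at T0. The SD of that T0 difference is √(2/129.6) = 0.124 SD units, and 0.124/0.35 = 0.35. A one-SD chance imbalance therefore separates the two unadjusted estimates by about a third of the planned effect. The randomisation section describes permuted blocks and mentions no stratification by baseline severity, so this is left to chance. ANCOVA corrects for it.

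**6. Effect on the SMD.** If the SMD were divided by the SD of change, a T1-scale d of 0.35 would become 0.35/√1.4 = 0.30 at r = 0.3 and 0.35/√0.6 = 0.45 at r = 0.7.

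**The case against.** The case against is substantial, and several parts of it stand.

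- **The sentence is ambiguous.** It names no change score and no group-by-time term, and it does not exclude a covariate. A model of T1 on group and T0 would fit the wording. A reader might infer that the plan definitely tests change and leaves T0 out; the article does not support that. Silence on a covariate is not exclusion.
- **Model detail can sit in an unshown SAP.** True of a covariate list. It does not remove the mismatch between the outcome definition and the analysis sentence, both of which are in this article.
- **The SMD at T1 does appear in the analysis section**, since SMDs are promised at every assessment. This softens the mismatch, but the sentence naming the test still refers to pre- and post-assessment.
- **The treatment contrast is the same.** A reader might infer that two different treatment effects are being estimated, or that one is biased. Randomisation makes the expected difference in change equal to the expected difference at T1. The hypothesis wording also fits either form.
- **The basis of d is not stated.** That the trial was powered on the T1 score is an inference from the outcome definition; the sample-size section gives only d and a t-test.
- **High correlation favours change over the T1 score.** Above r = 0.5 it beats the plain T1 comparison, and ANCOVA then adds little (0.976 to 0.989 at r = 0.7).
- **Equal SDs may not hold.** Entry at PHQ-9 ≥ 5 may narrow the T0 spread. If the T0 SD were 0.8 of the T1 SD (an assumption), the change variance is 1.64 − 1.6r. Change then breaks even with T1 at r = 0.4, and its power at r = 0.3 is 0.833 rather than 0.767.
- **259 is a complete-case count**, whereas the plan specifies ITT with multivariate imputation. The last three columns of the table show that the ranking is the same at 282.

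**Conclusion.** The point holds as a mismatch with a free improvement attached, not as a demonstrated error or a demonstrated loss of power. The outcome is defined at T1, the primary test is worded as a pre-post difference, and no baseline adjustment is named. The consequences are lower precision than the data allow, exposure to chance imbalance, and no single fixed primary p-value.

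At 259 evaluable, moving from a change score to ANCOVA raises power from 0.77 to 0.90 at r = 0.3, but only from 0.98 to 0.99 at r = 0.7. Moving from the unadjusted T1 score raises it from 0.88 to 0.90 and 0.99 respectively. These sizes rest on equal SDs, on d in T1 SD units and on an assumed r. The ranking is firmer: the choice has to be made before r is known, and ANCOVA is best at every value examined, whichever unadjusted analysis the sentence was meant to describe.

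**What to change.** Replace the primary-test sentence in Clinical analyses with wording such as: *The primary analysis is a linear model of QIDS-SR16 at T1 on randomised group, with QIDS-SR16 at T0 as a covariate; the adjusted mean difference at T1 is the primary effect.* This is a special case of the model family already named, so it also serves if ANCOVA was intended all along.

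State one SD as the SMD denominator, consistent with the T1 SMD in Table 1, footnote a. The pooled SD of the T1 scores fits most directly. The SD of change would not fit, and nothing in the article calls for a baseline SD.

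Use the same form for the continuous secondary outcomes, each adjusted for its own T0 value. If an SAP exists, align it with this sentence.

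The cost is a wording change and one degree of freedom. T0 QIDS-SR16 is already collected before randomisation, so no new data are needed.

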#### Economic evaluation

The health-economic evaluation will involve a combination of a cost-effectiveness analysis (CEA) and a cost-utility analysis (CUA). The economic evaluation will be performed from a societal perspective (all relevant costs) and a public health care perspective (only direct medical costs) with a time horizon of 36 months. In the cost-effectiveness analysis, the incremental cost-effectiveness ratio (ICER) will be based on the incremental costs per unit of effect gained (e.g. reliably improved case based on RCI). The corresponding equation is ICER = (Costs_IG_– Costs_CG_)/(Effects_IG_– Effects_CG_), where Costs are the annual per-participant costs and Effects are the unit of effect in IG and CG. In the CUA, the ICER will be expressed as incremental costs per quality adjusted life year (QALY) gained as based on the AQoL-8D. Sampling uncertainty in the ICER will be handled using nonparametric bootstrapping by resampling on patient-level. In addition, confidence intervals for ICERs will be obtained by bootstrapped quantiles. The bootstrapped ICERs will be plotted in a cost-effectiveness plane where the horizontal axis reflects differences in effects and the vertical axis differences in costs. The bootstrapped ICERs will also be shown in a cost-effective acceptability curve disclosing the probability that the intervention is cost-effective for a range of willingness-to-pay ceilings. To test the robustness of the base-case findings, multi-way sensitivity analyses will be done. Several assumptions made in the base-case scenario (e.g. about cost prices and volumes) will be changed to assess their impact on the ICERs.

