## Discussion

This study will be the first to investigate the clinical and cost-effectiveness of a tailored, guided IMI program for the prevention of depression and the reduction in depressive symptom severity in green professions.

The proposed study is characterized by several strengths. First, participants are provided with an IMI program with the option of engaging in an IMI tailored to individual needs. This might enlarge the reach of preventive IMIs by avoiding the exclusive label of depression and associated stigma. Further, this participatory and patient-centred approach might improve therapy motivation, if symptomatology has a clinical burden and psychotherapy is indicated. Also, the addressing of beliefs and needs of participants in form of a tailored and complaint-centred IMI program might strengthen treatment credibility. Intrinsic motivation and treatment credibility have been shown to positively relate to treatment adherence [34, 35]. Thereby, this complaint-based approach might be able to improve the overall impact of preventive internet-based interventions in routine health care by a) increasing the uptake of a preventive IMI program and b) by improving adherence to the IMI program. A large-scale dissemination is especially in prevention context highly desirable to reduce overall depression burden in population as well as associated health care costs. If proven effective, further studies could evaluate the proposed IMI program regarding its reach compared to single IMIs build, labelled and advertised solely as a depression prevention intervention. Second, we will be able to investigate long-term effectiveness of the IMI program. Previous research yielded few and inconsistent results regarding long-term efficacy of psychological interventions for subthreshold depression [18] and IMIs in particular [26]. This study will not only evaluate positive treatment effects, but also possible side effects of the IMI program. Since side effects of preventive IMIs in both short and long terms have not been sufficiently explored yet, this study will be able to provide a detailed understanding about positive and negative treatment effects of the proposed IMI program. Third, we will be able to conduct long-term cost-effectiveness analyses over a 36-month period. Evaluation of a guided IMI for depression prevention has already been shown to yield acceptable cost-effectiveness in preventing onset of clinical depression in people with subthreshold depression over a 12-month evaluation period [56]. However, cost-effectiveness might be less pronounced over a longer follow-up period [56] since results of a first meta-analytic review indicate that effectiveness of psychological interventions for prevention of depression might decline with longer follow-up periods [19]. The present study aims to yield first results regarding cost-effectiveness of an IMI program for prevention of depression over an extensive follow-up period of 36 months to close this knowledge gap. Forth, as a unique feature of the present trial, (cost)effectiveness of an IMI program provided in routine health care provided by the service provider GET.ON will be examined. Based on the pragmatic setting, this effectiveness trial is characterized by high external validity and generalizability regarding the target group of green professions [118, 119]. The efficacy of the employed IMIs in reduction of depressive symptomology has already been demonstrated in previous studies [23–25, 48–55]. For the present trial, the IMI program has been adapted to the context of green professions by the service provider to evaluate effectiveness in routine health care of the target group. Effectiveness and cost-effectiveness is especially interesting against the background of ongoing implementation of this IMI program into standard health care. Thereby, the present trial evaluates clinical and cost-effectiveness of a prospective supply situation in German preventive health care.

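### Bootstrap quantiles of the ICER are planned as its confidence interval without a condition on the sign of the effect difference; they lose meaning when a non-negligible share of replicates has zero or negative effect

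*Protocol article*

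**What the plan says.** The Economic evaluation section of the protocol article defines the ICER as the cost difference between the arms divided by their effect difference. One analysis uses a clinical unit of effect, with reliably improved cases as the example. The other is expressed as "incremental costs per quality adjusted life year (QALY) gained as based on the AQoL-8D". The evaluation runs "with a time horizon of 36 months".

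On uncertainty it says: "Sampling uncertainty in the ICER will be handled using nonparametric bootstrapping by resampling on patient-level". It then adds that "confidence intervals for ICERs will be obtained by bootstrapped quantiles". Two displays follow: "The bootstrapped ICERs will be plotted in a cost-effectiveness plane" and "The bootstrapped ICERs will also be shown in a cost-effective acceptability curve".

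The section attaches no condition to the quantile interval for replicates with a negative or near-zero effect difference. It names neither a Fieller interval nor an interval for net benefit. The protocol gives no expected QALY difference, cost difference or standard deviation for either.

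**The concern.** An ICER can be read only together with the signs of its two parts. A negative value arises when the programme is cheaper and better (dominant) and also when it is dearer and worse (dominated). A positive value arises when it is dearer and better (north-east quadrant) and also when it is cheaper and worse (south-west). As the effect difference approaches zero, the ratio runs off to plus or minus infinity.

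Taking the 2.5th and 97.5th percentiles of sorted ratios assumes that position on the number line reflects how favourable a result is. If replicates fall on both sides of zero effect, it does not. The best and worst results can then share one tail, and the two limits do not enclose a set of plausible ICERs.

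Cost-effectiveness is in the trial's title and is one of its research questions, and the Discussion links it to routine implementation. An interval printed beside the ICER is likely to be quoted on its own.

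**Working it through.** **Inputs.** The section reports no economic figure that could be reproduced. From the Sample size section come the target of 360 participants, the 1:1 allocation and the 28% dropout, which leaves 360 × 0.72 ≈ 259. The same section assumes d = 0.35 for depressive symptom severity. The standardized QALY effect is not given, so it is assumed over the range 0.05 to 0.35.

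**Step 1: when ordering holds.** Write dE and dC for the effect and cost differences in a replicate, and λ for willingness to pay. If dE > 0, then dC/dE ≤ λ is the same statement as λ·dE − dC ≥ 0. With all replicates at dE > 0, whether dC is positive or negative, the ratio quantiles therefore still act as limits on willingness to pay. If dE < 0 the inequality reverses and the ranking breaks. The condition that matters is the sign of the effect difference, not whether all replicates lie in one quadrant.

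**Step 2: how often dE crosses zero.** With a normal approximation and equal arms, the expected ratio of estimate to standard error is k = d·√(N/4).

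- If the estimate equals the assumed effect, the share of replicates below zero is Φ(−k).
- The probability that the trial yields more than 2.5% of such replicates is Φ(1.96 − k).

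Example: d = 0.10 and N = 360 give k = 0.10 × √90 = 0.949, so Φ(−0.949) = 17% and Φ(1.011) = 84%.

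| Assumed standardized QALY effect | Share below zero, N = 360 | P(more than 2.5% below zero), N = 360 | Share below zero, N = 259 | P(more than 2.5% below zero), N = 259 |
|---|---|---|---|---|
| 0.05 | 32% | 93% | 34% | 94% |
| 0.10 | 17% | 84% | 21% | 88% |
| 0.20 | 2.9% | 52.5% | 5.4% | 64% |
| 0.35 | 0.04% | 9% | 0.2% | 20% |

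**Step 3: what the interval looks like.** All figures here are assumed: dE = 0.03 QALY with SE 0.02, dC = EUR 300 with SE 1,500, independent normal draws.

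- Point ICER: 300/0.03 = EUR 10,000 per QALY.
- Quadrant shares: north-east 54%, south-east 39%, north-west 3.9%, south-west 2.8%.
- Ratio quantiles: roughly EUR −300,000 to +343,000 per QALY.
- Of the replicates below the lower limit, about 49% are dominant and 51% dominated.
- Net benefit at EUR 20,000 per QALY: 20,000 × 0.03 − 300 = EUR 300. Its SE is √((20,000 × 0.02)² + 1,500²) = 1,552, so the 95% interval is 300 ± 1.96 × 1,552, about EUR −2,740 to +3,340. This interval is finite and ordered.

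**Step 4: the contrast.** Keep everything but reduce the effect SE to 0.0075, so that only about 0.003% of replicates fall below zero effect. The ratio quantiles are still wide, about EUR −99,000 to +126,000, because the assumed cost SE is large. But over 99.9% of the replicates below the lower limit are now dominant, so the interval is ordered and usable. Width alone is not the defect. The mixing of opposite results in one tail is.

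**The case against.** Four arguments carry weight.

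- **Already covered.** The quantile interval is introduced as an addition. The same section commits to the plane, the acceptability curve over a range of ceilings, and sensitivity analyses. The plane and curve remain valid across quadrants, and the curve already gives the probability of positive net benefit at each threshold. This stands and limits the harm, but it does not make the printed interval correct.
- **Left to the analysis plan.** A condensed article may leave the handling of awkward replicates to a fuller document. That would be a good answer had the article only promised intervals. It names the method, and as worded the method has no safeguard.
- **One quadrant.** A reader might infer that the interval fails unless every replicate lies in a single quadrant. That is too strict. Crossing zero in cost alone leaves the ordering intact, and a one-quadrant rule would suppress usable intervals.
- **Likelihood and harm.** A reader might also infer that crossing is the expected outcome here, or that a probably cost-effective programme would be made to look uncertain. The documents support neither. The likelihood depends on a QALY effect that they do not give. The Discussion says only that "effectiveness of psychological interventions for prevention of depression might decline with longer follow-up periods", which makes a small effect plausible but does not establish it. In the illustration the probability of positive net benefit is about 58% (300/1,552 = 0.19 SE), so that programme is uncertain on any measure.

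**Conclusion.** The point holds in limited form. As stated, the rule can yield an interval without meaning, and it does so when a non-negligible share of replicates has an effect difference at or below zero. With 360 participants, the chance of more than 2.5% such replicates runs from 93% at an assumed standardized QALY effect of 0.05 to 9% at 0.35, and is about even at 0.20. With 259 it runs from 94% to 20%. The problem becomes improbable only if QALYs over 36 months show an effect about as large as the one assumed for depressive symptoms at nine weeks.

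These figures rest on an assumed effect range and a normal approximation to the bootstrap distribution. N = 259 applies the protocol's dropout figure to the 36-month data without credit for the planned imputation.

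Severity is modest. This is a supplementary interval in a secondary analysis, and the plane and acceptability curve are sound. The primary analysis and the sample size are not affected.

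**What to change.** Replace the sentence on quantile intervals with a reporting rule that uses the same bootstrap replicates:

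- report the 95% interval of incremental net monetary benefit, λ·dE − dC, at a few willingness-to-pay values stated in advance;
- report separate 95% intervals for incremental costs and incremental effects, and the share of replicates in each quadrant;
- keep the planned plane and acceptability curve;
- give an interval for the ICER itself only when essentially all replicates have a positive effect difference, or give a Fieller interval when it is bounded (estimated effect difference more than 1.96 SE from zero).

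Apply the rule to both the cost-effectiveness and the cost-utility analysis. The cost is a change of wording and a few extra summary lines. No new data, participants or resampling are needed.
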